To date there is no literature on the combined effects of *B. breve* M-16V, scGOS/lcFOS and L-glutamine in preterm infants nor their impact on neonatal brain development. However a recent preclinical trial with preterm born piglets (*n* = 40) showed those supplemented with *B. breve* M-16V, scGOS/lcFOS and L-glutamine demonstrated increased cognitive performance as assessed in the T-maze compared to control piglets [50]. Additionally, on ex vivo diffusion imaging piglets in the intervention group showed increased maturation of the white matter fibre bundles and advanced grey matter microstructural maturational processes compared to control piglets [50]. We hypothesize that this combination of probiotics, prebiotics and L-glutamine may act synergistically and will therefore combine these components in this study. We hypothesize that scGOS/lcFOS will promote survival of *B. breve* M-16V and improve its effect on immunomodulation and intestinal integrity in addition to its expected intrinsic benefits. L-glutamine may further enhance these favourable effects. This combination may decrease serious neonatal infections and subsequently reduce white matter injury. This study aims to evaluate the benefits of *B. breve* M-16V, scGOS/lcFOS and L-glutamine on white matter microstructure integrity (i.e., development of white matter tracts) at term equivalent age in very and extremely preterm born infants.

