**Inclusion criteria**	
1) Gestational age of 24 + 0 to < 30 + 0 weeks	
2) Less than 72 h old and the intention to receive the first administration of study product between 48 and 72 h after birth	
3) Written informed consent from custodial parent(s)	

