### Supplementation

Study product supplementation will start between 48 and 72 h after birth or, if the infant is clinically unstable as soon as possible thereafter, and will continue until 36 weeks postmenstrual age. If the infant is discharged home or fully breastfed before 36 weeks postmenstrual age supplementation will be stopped. Study product Part A will be administered enterally once per day as a single daily dose not supplemented to feeding or medication. The dosage of *B. breve* will depend on birth weight: Infants with a birth weight ≥ 1000 g will receive 3 × 10^9^ colony-forming units (cfu) per day; Infants with a birth weight < 1000 g will receive 1.5 × 10^9^ cfu per day, to be increased to 3 × 10^9^ cfu per day when they have reached enteral feeding intakes of 50 ml/kg/day. Study product Part B will be administered enterally supplemented to the regular milk feed (breast milk or preterm formula, depending on parents’ choice). Dosage will be increased in a stepwise fashion. Based on the infant’s weight, daily intake of enteral feeding and the desired (maximum) osmolarity of the feeding, a supplementation schema was created, starting with a minimum dosage of 0.05 g/day L-glutamine and 0.1 g/day scGOS/lcFOS and aiming for a final dose of 0.3 g/kg/day L-glutamine and 0.6 g/kg/day scGOS/lcFOS when the infant receives full enteral feeding (120 ml/kg/day for 1 day). The final dosages of L-glutamine and scGOS/lcFOS were based on the GEEF study [45] and CARROT study [51], respectively, in which supplementation was well tolerated.

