#### Secondary outcomes

White matter injury, measured with the white matter injury score according to Kidokoro et al., [57] which evaluates cystic lesions, focal signal abnormality, myelination delay, thinning of the corpus callosum, dilated lateral ventricles and volume reduction on T2- and T1-weighted MR images acquired at TEA.Brain tissue volumes (cerebellum, cortical grey matter, unmyelinated white matter, deep nuclear grey matter, ventricular volumes and extracerebral cerebrospinal fluid) and cortical morphology (sulcation index, cortical surface area and cortical thickness) assessed using the segmentation method of Moeskops et al. [58] of T2- and T1-weighted MR images made at TEA.The occurrence of serious neonatal infections (defined as culture proven or clinical sepsis with associated clinical symptoms; clinically significant NEC [i.e., Bell’s stage two or higher]; meningitis with or without positive culture; or pneumonia [positive culture of tracheal aspirate, bronchial secretion, or sputum positive for microorganisms with associated clinical symptoms]) [45, 51] until TEA.Serum concentrations of specific circulating inflammatory markers such as IL-6, IL-10, TNF-α and IL-8/CXCL8 measured with flow cytometry and Luminex at 7, 21 and 42 days postnatal, 30 and 36 weeks postmenstrual age, discharge to other hospital and TEA (optional, in a subgroup).Motor and cognitive development assessed with the Bayley Scales of Infant and Toddler Development, Third Edition, [59] at 24 months corrected age.

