### Data collection

All study data will be collected in a validated eCRF (VIEDOC, from Pharma Consulting Group during the intervention period; Castor during the follow up period). To guarantee data quality only trained study staff can enter data in the eCRF. Data will be collected and stored in line with data privacy laws, and details on data management are documented in the data management plan. Collected data will include: gender, GA, (birth) weight, (birth) length, (birth) head circumference, parental level of education, parental head circumference, score for Neonatal Acute Physiology – Perinatal Extension (SNAPPE-II), obstetric and perinatal details (such as presence of chorioamnionitis, prenatal medication, relevant maternal illnesses, Apgar scores and cord blood parameters), neonatal morbidity (such as infant respiratory distress syndrome, need for respiratory support, neonatal infections, patent ductus arteriosus, intraventricular haemorrhage and post haemorrhagic ventricular dilatation), neonatal medication, enteral and parenteral feeding characteristics and cumulative intake. Additionally stool samples will be collected at fixed time points to evaluate bacterial colonisation and the development of the microbiome and to be able to detect possible cross contamination with *B. breve* M-16V in infants allocated to the control group, using *B. breve* M-16V specific primers.

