### Statistical analysis

#### Primary outcome parameter and other MRI-derived parameters

TBSS analysis will be performed as previously described [61]. In summary, group comparisons will be performed with FMRIB Software Library’s Randomise tool using a general linear univariate model, [62] with family-wise error correction for multiple testing using threshold-free cluster enhancement with a significance level of *p* < 0.05 [63]. Group comparisons for volumetric analyses will be performed with ANOVA, with false discovery rate to correct for multiple testing. In all analyses GA at birth, postmenstrual age at time of MRI, birth weight Z-score and days of ventilation will be entered as covariates. These analyses have been used in several other observational and intervention studies conducted in the UMC Utrecht and other research groups, in preterm infants at TEA (mean and median GA of 28.7 weeks), [52, 64] healthy and asphyxiated full term infants, [65, 66] as well as children at school age (7.5–8.5 years and 12 years of age) [67–69].

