## Discussion

Infection and inflammation, together with ischemia, play an important role in white matter injury. These processes cause upregulation of pro-inflammatory cytokines and activate microglia. Together this leads to excitotoxicity and free radical attack, causing cell death of premyelinating oligodendrocytes and subsequent glial scarring of the white matter [70]. It is therefore likely that reduction of infectious morbidity may have a positive effect on brain integrity through less disturbance of white matter structure. Multiple possible mechanisms contribute to the proposed effect of probiotics, prebiotics and L-glutamine on infectious morbidity. The bacterial colonisation of the gastrointestinal tract affects the immune system through several pathways [71] including the production of immunomodulatory factors such as short chain fatty acids [72]. Production of short chain fatty acids by intestinal bacteria is essential for numerous brain functions, such as microglia maturation and function [73] and maintaining integrity of the blood-brain-barrier [74]. Another postulated mechanism is one of improved white matter integrity through direct interaction with immune cells. *B. breve* attenuates the pro-inflammatory response in mouse macrophages in vitro [75]. As described previously probiotics, prebiotics and L-glutamine regulate bacterial colonisation, improve intestinal mucosal integrity and decrease bacterial translocation. This shifts the immune system to a more anti-inflammatory phenotype, indeed enteral supplementation of prebiotic fibers has been shown to decrease systemic cytokine levels (IL-1β, IFN-γ and TNF-α) in preterm infants at day 7 of life [41].

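### The primary FA model and the volumetric models adjust for total days of ventilation, a post-randomisation variable, so they would not estimate the total effect if the product alters ventilation time

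*Protocol article*

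**What the plan says.** The covariate rule is in the protocol article under Statistical analysis, Primary outcome parameter and other MRI-derived parameters: "In all analyses GA at birth, postmenstrual age at time of MRI, birth weight Z-score and days of ventilation will be entered as covariates". It covers the voxelwise TBSS comparison of FA, which is the primary outcome, and the ANOVA comparisons of brain volumes. The section gives no time window for counting ventilation days and names no MRI analysis without them.

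On timing, Table 1 requires infants to be "Less than 72 h old and the intention to receive the first administration of study product between 48 and 72 h after birth". Under Supplementation, "Study product supplementation will start between 48 and 72 h after birth", or as soon as possible thereafter if the infant is unstable, and supplementation "will continue until 36 weeks postmenstrual age" unless the infant is discharged home or fully breastfed earlier.

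On mechanism, the Background (end of the L-glutamine section) says: "This combination may decrease serious neonatal infections and subsequently reduce white matter injury". The Discussion adds: "It is therefore likely that reduction of infectious morbidity may have a positive effect on brain integrity through less disturbance of white matter structure". The infections counted under Secondary outcomes are sepsis, NEC, meningitis, "or pneumonia [positive culture of tracheal aspirate, bronchial secretion, or sputum positive for microorganisms with associated clinical symptoms". Data collection lists, as one group, "neonatal morbidity (such as infant respiratory distress syndrome, need for respiratory support, neonatal infections" and other conditions.

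**The concern.** Randomisation protects the comparison of arms when the model contains only variables that the product cannot have changed. Total days of ventilation is not such a variable by its timing. If the product prevents some sepsis or pneumonia and those infants then need less ventilation, part of any benefit on FA runs through ventilation, and holding ventilation constant removes that part. In addition, illness severity probably drives both ventilation time and FA. Once the product affects ventilation, conditioning on it also links arm to severity, which randomisation had kept apart.

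What is at stake is the meaning of the primary result. The stated aim is the effect of the product on white matter integrity. The fitted coefficient would answer a narrower question, the effect at equal ventilation time, and even that only if there were no unmeasured common causes.

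**Working it through.** **1. Timing.** Randomisation takes place before 72 h, so at most 3 days of ventilation can precede it. Supplementation is planned to 36 weeks postmenstrual age. That is up to 36 − 24 = 12 weeks after birth for the youngest infants and about 36 − 30 = 6 weeks for the oldest. Any count above 3 days must include days after randomisation.

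**2. Pathway.** The documents state two links: product to fewer serious infections, and fewer infections to better white matter. They do not state a link from product or infection to ventilation time. That link is an inference from the infection definition, which includes sepsis and a respiratory infection, and from the listing of respiratory support among the neonatal morbidities.

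**3. Form of the bias.** The plan has no figure of its own on this point to reproduce. Its 35 evaluable infants per group comes from published TBSS simulations, without an SD or a power. The following is therefore an illustration for one standardised FA measure, and every parameter is assumed:
- T = total effect of the product on FA, in SD
- a = reduction in ventilation days caused by the product, in SD of ventilation days
- b = fall in FA (SD) per SD of ventilation
- u = loading of unmeasured severity on both ventilation and FA

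With ventilation days in the model, the expected coefficient is

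adjusted effect = T − a × (b + u²).

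The term a × b is the mediated part, and a × u² comes from the shared severity. Both vanish when a = 0. Without ventilation days the model estimates T.

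**4. Numbers.** Take T = 0.68 SD, which has about 80% power with 35 per arm on a single two-sided 5% t-test. Use (b, u) = (0.3, 0), (0.5, 0) and (0.3, 0.4), so that b + u² = 0.30, 0.50 and 0.46. Power is from simulation.

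| a (SD) | Adjusted effect | Shortfall | Power, adjusted | Power, without ventilation |
|---|---|---|---|---|
| 0 | 0.68 | none | 84–89% | about 80% |
| 0.2 | 0.58–0.62 | 9–15% | 76–77% | about 80% |
| 0.4 | 0.48–0.56 | 18–29% | 60–65% | about 80% |

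Example: a = 0.2 and b + u² = 0.50 give 0.68 − 0.10 = 0.58, and 0.10/0.68 = 15%.

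The error need not be conservative. If the product lengthened ventilation (a = −0.2), the same formula gives 0.74–0.78, an overstatement. If T = 0 but a = 0.2, the adjusted coefficient is −0.06 to −0.10, and the simulated rejection rate is 6–8% instead of 5%.

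**5. How large might a be?** The documents offer only loose anchors. One is late-onset sepsis of about 27% in infants of 1000 g or less (Discussion). The other is a relative risk of 0.76 for invasive infection with enteral glutamine (Background). Together they give a risk difference of 0.27 × (1 − 0.76) = 0.065. If each infection added 1 SD of ventilation (assumed), then a = 0.065. The shortfall is then 0.065 × 0.30/0.68 = 3% to 0.065 × 0.50/0.68 = 5%, and simulated adjusted power is 81–86% against about 80%. Shifts of 0.2 SD and 0.4 SD would need each infection to add about 0.2/0.065 = 3 SD and 0.4/0.065 = 6 SD of ventilation, or a larger reduction in infections, or another route to ventilation.

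**The case against.** The strongest reply is that bias needs the product to change ventilation time, and nothing in the documents says that it does. The Discussion also describes routes that need not involve ventilation: short-chain fatty acids acting on microglia and the blood–brain barrier, and direct interaction with immune cells. If ventilation is unaffected, the covariate is harmless and useful (84–89% power against about 80% in the illustration). With the modest shift in step 5, its gain in precision roughly offsets or exceeds the shrinkage. All of this stands, and it limits how strongly the point can be put.

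A reader might infer that the primary estimate is biased, or that the trial loses a definite share of its power. The documents support neither. The first assumes an effect on ventilation that is only plausible. The second needs an FA standard deviation, a power and ventilation data, none of which is given. It would also be wrong to shrink the effect and leave the residual variance unchanged, because a prognostic covariate reduces that variance.

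Two further replies carry less weight. The article notes that these analyses were used in earlier observational and intervention studies. In observational work, however, ventilation days can be a confounder to remove, whereas here they may be a consequence of the randomised product. The article also defers details to a statistical analysis plan that is not shown, and that plan may define a counting window or add a sensitivity analysis. But the covariate is stated here as a rule for all the MRI analyses, so this is a stated choice and not an omitted detail.

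**Conclusion.** The point stands in conditional form. Adjusting the primary FA model and the volumetric models for total days of ventilation makes their validity for the total randomised effect depend on the product not changing ventilation time. The protocol does not state that assumption, and its own hypothesis of fewer serious infections makes it doubtful.

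Size and direction cannot be fixed from the documents. Under the assumed linear model the distortion is a × (b + u²): nothing if the product leaves ventilation alone, about 3–5% of a 0.68 SD effect at the loose anchors above, and 9–15% at a 0.2 SD shift. The power figures are for a single-measure t-test and only approximate a voxelwise TBSS analysis with family-wise correction.

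The reason to change the rule is that it alters what the primary analysis estimates. No demonstrated loss of power is claimed.

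**What to change.** Before unblinding:
- Remove total days of ventilation from the primary TBSS model and the volumetric models.
- Keep GA at birth and birth weight Z-score. Keep postmenstrual age at MRI as a scan-timing variable.
- If adjustment for severity is wanted, use only severity measured before first product: SNAPPE-II, which Data collection already lists, and/or ventilation status or days up to randomisation. State that the chosen measure is fixed before first product.
- Report the model with total ventilation days only as a labelled sensitivity or exploratory mediation analysis.

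The change is a sentence or two in the analysis plan and needs no extra infants. SNAPPE-II is already collected; ventilation up to randomisation needs dated respiratory-support records. The cost is some precision if total ventilation days predict FA better than the baseline measures. In the illustration, dropping ventilation days with no replacement and a = 0 costs 4–9 percentage points of power, and a good baseline severity measure would recover part of that.

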#### Safety and tolerance parameters, exploratory outcome parameters and secondary outcome parameters that are not derived from MRI assessment

Statistical analysis of continuous outcomes that are measured at more than one time point will be performed by means of linear mixed models analysis. Statistical analysis of discrete outcomes (dichotomous variables, ordered categorical variables and counts) will be performed using parametric (i.e., generalized linear models) or non-parametric methods. For other types of outcome parameters stratified tests (e.g., Cochran-Mantel-Haenszel test) and/or simple hypothesis testing methods (e.g., Chi-square or Fisher exact tests) will be employed. Details on the statistical analyses will be documented in a statistical analyses plan prior to database lock/unblinding.

Considering our relatively small sample size, it is possible that confounding factors for probiotic efficacy, such as antibiotic exposure, could be unevenly distributed between the active and placebo study group. Baseline characteristics will be evaluated at the start of the statistical analysis, and important confounding factors will be taken into account as covariates in the analysis. Analysis of the primary outcome parameter will be based on all included patients intended to treat with usable MRI according to DTI quality. Additionally, a per protocol analysis will be carried out for supporting purposes. Safety parameters will be analysed on the All Subjects Treated population. To account for possible cross contamination additional analyses will be performed to evaluate infants with and without *B. breve* M-16V colonisation. A *p*-value < 0.05 will be considered statistically significant.

## Discussion

Infection and inflammation, together with ischemia, play an important role in white matter injury. These processes cause upregulation of pro-inflammatory cytokines and activate microglia. Together this leads to excitotoxicity and free radical attack, causing cell death of premyelinating oligodendrocytes and subsequent glial scarring of the white matter [70]. It is therefore likely that reduction of infectious morbidity may have a positive effect on brain integrity through less disturbance of white matter structure. Multiple possible mechanisms contribute to the proposed effect of probiotics, prebiotics and L-glutamine on infectious morbidity. The bacterial colonisation of the gastrointestinal tract affects the immune system through several pathways [71] including the production of immunomodulatory factors such as short chain fatty acids [72]. Production of short chain fatty acids by intestinal bacteria is essential for numerous brain functions, such as microglia maturation and function [73] and maintaining integrity of the blood-brain-barrier [74]. Another postulated mechanism is one of improved white matter integrity through direct interaction with immune cells. *B. breve* attenuates the pro-inflammatory response in mouse macrophages in vitro [75]. As described previously probiotics, prebiotics and L-glutamine regulate bacterial colonisation, improve intestinal mucosal integrity and decrease bacterial translocation. This shifts the immune system to a more anti-inflammatory phenotype, indeed enteral supplementation of prebiotic fibers has been shown to decrease systemic cytokine levels (IL-1β, IFN-γ and TNF-α) in preterm infants at day 7 of life [41].

An important, well-known factor in microbiome development is the frequency and duration of antibiotic treatment. Preterm infants are regularly exposed to antibiotics for suspected infection. As spontaneous preterm birth itself could be an expression of infection antibiotic treatment is routinely started directly after birth in very and extremely preterm infants. Furthermore late onset sepsis (starting > 72 h after birth) is a common problem in very and extremely preterm infants, leading to additional antibiotic exposure. Even though the aim of antibiotic treatment is to diminish pathogenic bacteria beneficial bacteria are also affected, causing an altered microbiome development [76, 77]. Multiple studies have shown that (prolonged) antibiotic exposure leads to a less diverse microbiome [78–82]. We expect that the effect of our intervention will be influenced by exposure to antibiotics since courses of antibiotics will most likely diminish the growth of *B. breve*. We will include infants only in one hospital in which the incidence of late onset sepsis in extremely low birth weight infants (birth weight ≤ 1000 g) is approximately 27% [83]. Based on the previous intervention studies with probiotics, prebiotics and glutamine separately the intervention may also reduce the incidence of (suspected) infections, which may reduce the antibiotic exposure [25, 45, 51]. It is possible that the results of our study could be different in other hospitals with other antibiotic policies.

Our study will concern a very vulnerable, critically ill study population and the safety of the infants will be monitored very closely. Based on the results from previous studies with probiotics, prebiotics and L-glutamine as individual supplements no major side effects related to the study products are expected. The only recognised possible adverse reaction associated with probiotic administration is a positive culture of the probiotic organism from a normally sterile site. This is very rare and has never been reported with *B. breve* M-16V supplementation. For prebiotic supplementation in general mild gastrointestinal discomfort (loose stools, constipation, abdominal pain and flatulence) has been reported. However, in a recent systematic review and meta-analysis no safety concerns were raised from 18 evaluated randomised controlled trials on prebiotic supplementation in preterm infants [40]. No adverse events related to L-glutamine supplementation in preterm infants have been described [44–46, 48, 84]. For both prebiotic and L-glutamine supplementation the dosages that will be used in our study are equal to or below the dosages used in the previously mentioned studies.

This trial focusses on the effect of the active study product on brain development. Several important clinical outcomes, such as occurrence of serious infections, growth and neurodevelopmental outcome, are secondary or safety outcomes of this trial. We hope that our trial can serve as a first step in the development of future studies in which the effect of our active study product on clinical outcomes can be evaluated. To date we are not able to completely prevent perinatal brain injury in preterm infants. To our knowledge the NutriBrain study is the first to evaluate the effect of a combination of probiotics, prebiotics and L-glutamine on brain development in preterm infants. It may give new insights in the development and function of the gut microbiota and immune system in relation to brain development and may provide a new, safe treatment possibility with few potential side effects, to improve brain development in the care for preterm infants.

